### Recruitment

The patients will be recruited from hospitals located in the city of Porto Alegre and its metropolitan region. Patients with ARDS will be accessed from outpatient clinics, databases, or previous records of ICU admission due to ventilatory failure of patients undergoing clinical follow-up at the respective centers, and controls will be recruited from family members or people living with the patients. Telephone contacts will be made after hospital discharge, and the eligibility criteria and the free and informed consent form will be applied. With duly informed and signed consent, the following procedures will be performed: a review of medical records and structured telephone interviews and teleconsultation to assess eligibility and scheduling of previously specified exams.

### Procedures

All participants will undergo teleconsultation by telephone to evaluate possible contraindications for the following complementary exams: serum creatinine and urea, creatinine and total protein in urine, microalbuminuria and qualitative urinalysis; spirometry with pulmonary diffusion for carbon monoxide (CO_2_) without a bronchodilator test; treadmill ergospirometry with a ramp protocol; high-resolution tomography of the chest (noncontrast); and cardiac and renal magnetic resonance imaging with gadolinium contrast. Patients with contraindications to one or more exams who are eligible will remain in the study. Teleconsultation and exams will be performed between 12 and 36 months after discharge from the index hospitalization for ARDS or, for controls, at the time of inclusion (with a restricted window of up to 90 days due to the risk of controls developing COVID-19 or other clinical complications after the initial visit). Figure 2 is the flow chart of the participants in the study.

**Figure 2 f2:**
[figure not shown]
Trajectory of the study participants.

### Outcomes

The primary outcome of the study is the pulmonary diffusing capacity for carbon monoxide (DLCO) measured after 12 months. The following were considered secondary outcomes: physical-functional capacity measured by the modified Barthel index after 12 months;^(18)^ instrumental activities of daily living measured by the Lawton and Brody scale of instrumental activities of daily living from 12 months onward;^(19)^ muscle function and strength assessed by Strength, Assistance with Walking, Rising from a Chair, Climbing Stairs, and Falls (SARC-F) at 12 months of age;^(20)^ dyspnea measured by the modified *Medical Research Council* (MRC) dyspnea scale from 12 months of age;^(21)^ health-related quality of life assessed using the EuroQol 5 Dimensions 3 Levels questionnaire (EQ-5D-3L) from 12 months onward;^(22.23)^ ergospirometric variables from 12 months onward: direct oxygen consumption, maximum oxygen consumption (VO_2_ peak), minute volume/CO_2_ production ratio (VE/VCO_2_ slope) and oxygen uptake efficiency (OUES - Oxygen Uptake Efficiency Slope); spirometric variables from 12 months onward: vital capacity (VC), forced expiratory volume in one second (FEV1) and FEV1/VC; and radiological patterns of pulmonary fibrosis assessed by high-resolution tomography of the chest from 12 months onward; radiological patterns related to the sequelae of acute myocarditis assessed by cardiac magnetic resonance imaging with T1- and T2-weighted parametric maps and by means of the delayed enhancement technique from 12 months onward; radiological patterns of sarcopenia assessed by high-resolution tomography of the chest from 12 months onward; changes in renal function or structure assessed by magnetic resonance imaging and laboratory tests; and major cardiovascular events (non-fatal infarction, non-fatal stroke, acute heart failure) and thromboembolic events (deep venous thrombosis, pulmonary embolism) after hospital discharge. The data collection protocol for the exams collected is described in the Supplementary Material.

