#### Controls

Individuals ≥ 18 years of age who are family members or social interactors of participants who have survived ARDS due to COVID-19 will be considered controls. Individuals who are unwilling to undergo the proposed tests, have a history of persistent symptoms after SARS-CoV-2 infection, have a history of nonelective hospitalization due to clinical disease in the last 12 months, have a severe underlying disease with a life expectancy of less than 3 months, or do not consent to participate in the study will be ineligible. The following symptoms are considered persistent symptoms of COVID-19: cough, fatigue, muscle pain, dyspnea, anosmia, ageusia, and memory or concentration deficit, as previously evaluated by a physician and attributed to COVID-19.

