### Recruitment

The participating centers will select patients whose internal records show that they meet the inclusion criteria for participation in the study. Recruitment will be performed by face-to-face or remote interviews with the patient and/or his or her family by the research team. After they sign the informed consent form and after collection of their baseline data, the participants will be evaluated through a structured and centralized telephone interview. For ARDS/COVID-19 patients, the interview will be conducted 12 months after hospital discharge, and controls will be evaluated within 90 days after their inclusion in the study.

The participants will be included by applying the eligibility criteria, which will be recorded in the triage log. Patients who meet all the inclusion criteria and no exclusion criteria will be invited to voluntarily participate in the study by signing the informed consent form in person or electronically. The process of obtaining informed consent will be detailed in the ethics and good clinical practices section. The participant will be approached by a researcher duly trained in good clinical practice, who will maintain the anonymity and confidentiality of the data and will promote conditions of comfort for the participant.

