### Statistical analysis

The variables will be described as n (%) for qualitative variables, mean ± standard deviation for symmetric quantitative variables, and median (interquartile range) for asymmetric quantitative variables. The distribution of quantitative variables will be assessed by graphical visualization of histograms and the Shapiro–Wilk test. The primary outcome will be compared between the study groups using logistic regression adjusted for sex, age, and comorbidities. The reported measure of effect will be the odds ratio (OR) with its 95% confidence interval (95%CI). The secondary outcomes with qualitative distributions will be evaluated in the same way as the primary outcome. The quantitative distribution of secondary outcomes will be evaluated by means of multiple linear regression adjusted for sex, age, and comorbidities. The reported measure of effect will be the difference in means with their 95%CIs. P values < 0.05 will be considered statistically significant. Secondary outcomes will not be adjusted for multiple variables. Thus, the findings for the secondary outcomes will be interpreted as exploratory. The analyses will be performed with R software packages to be detailed at the time of analysis.^(25)^

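### Events timed from hospital discharge would, on a literal reading, be compared with controls who have no discharge date and are screened on recent admissions, which biases the odds ratio upward

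*Protocol article*

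**What the plan says.** The Outcomes section lists, as the last secondary outcome, "major cardiovascular events (non-fatal infarction, non-fatal stroke, acute heart failure) and thromboembolic events (deep venous thrombosis, pulmonary embolism) after hospital discharge".

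The Statistical analysis section sets out logistic regression for the primary outcome, adjusted for sex, age and comorbidities and reported as an odds ratio with 95% CI. It then states: "The secondary outcomes with qualitative distributions will be evaluated in the same way as the primary outcome". No outcome is exempted, and no term for observation time is mentioned. Secondary findings are labelled exploratory.

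The two groups are observed differently:

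- **Controls, eligibility.** They are relatives or social contacts of the patients, and are ineligible if they "have a history of nonelective hospitalization due to clinical disease in the last 12 months". The Abstract is broader and refers to any hospitalization in that period.
- **Controls, timing.** "controls will be evaluated within 90 days after their inclusion in the study" (the second Recruitment section). The Procedures section justifies the short window by "the risk of controls developing COVID-19 or other clinical complications after the initial visit".
- **Patients, eligibility.** The exclusion list for ARDS patients has nothing on readmission or events after discharge.
- **Patients, timing.** The Procedures section says "Teleconsultation and exams will be performed between 12 and 36 months after discharge from the index hospitalization for ARDS", whereas the second Recruitment section says "the interview will be conducted 12 months after hospital discharge" and the Abstract also gives 12 months.

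**The concern.** A between-group odds ratio for a binary event is interpretable only if both groups could have had the event over comparable time and neither was selected on having had it. Neither condition holds here.

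Controls have no index discharge, so the outcome definition gives them no start of risk. Infarction, stroke, acute heart failure and pulmonary embolism usually lead to a nonelective admission. A control with such an admission in the past year cannot enter the study, while a patient with the same event after discharge can. Adjustment for sex, age and comorbidities does not undo selection on the outcome, and logistic regression treats 12 months and 36 months of exposure alike.

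At stake is a reported odds ratio that looks like excess cardiovascular and thromboembolic risk after ARDS, on a topic that the Discussion raises explicitly, when part or all of it could come from how controls are chosen and observed.

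**Working it through.** **The plan's own figure.** The document gives no event rate, power or sample size for this outcome. Its DLCO calculation reproduces: n = 2 × (1.96 + 0.8416)² × 5² / 2² = 2 × 7.849 × 6.25 = 98.1, so 99 per group, and 99 / 0.9 = 110. I use 110 per group below.

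**Inputs from the document.** Patient window T = 1 year (Abstract, second Recruitment section) up to 3 years (Procedures). Control evaluation within 90 days of inclusion. Control exclusion for nonelective clinical admission in the last 12 months.

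**Assumptions, since the document gives none.** The same constant annual rate r in both groups (true odds ratio 1), with r = 2% and a range of 1% to 5%. Share h of events that cause a nonelective admission: 80% or 50%.

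**Formula.** With w the years in which a control event can still be counted, the risk is 1 − exp(−r·w) and the odds are exp(r·w) − 1. The apparent odds ratio is

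OR = [exp(r·T) − 1] / [exp(r·w) − 1].

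The control window is not stated, so three readings are needed:

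- (a) 90 days after inclusion only: w = 90/365.25 = 0.246.
- (b) the 12 months before inclusion: w = 1 − h.
- (c) a look-back equal to the patients' window: w = (T − 1) + (1 − h) = T − h.

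Patient odds at r = 2% are 0.02020, 0.04081 and 0.06184 for T = 1, 2 and 3.

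| Control window | T = 1 | T = 2 | T = 3 |
|---|---|---|---|
| (a) 90 days | 4.1 | 8.3 | 12.5 |
| (b) 12 months, h = 80% | 5.0 | 10.2 | 15.4 |
| (b) 12 months, h = 50% | 2.0 | 4.1 | 6.2 |
| (c) equal look-back, h = 80% | 5.0 | 1.7 | 1.4 |
| (c) equal look-back, h = 50% | 2.0 | 1.3 | 1.2 |

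Examples: (a), T = 1: 0.02020 / 0.00494 = 4.1. (c), T = 3, h = 50%: 0.06184 / 0.05127 = 1.2.

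**Sensitivity to the rate.** Between 1% and 5% a year the ratios barely move: (a) at T = 3 runs from 12.3 to 13.1, and (c) at T = 1 with h = 80% from 5.02 to 5.10.

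**When the direction reverses.** For a control look-back of L years (L at least 1), w = L − h, so the odds ratio falls below 1 only when L exceeds T + h. With L = 5 and h = 80% it is 0.23, 0.47 and 0.71 for T = 1, 2 and 3.

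**Sparse data.** Under (a) at 2% a year, 110 controls are expected to have 110 × [1 − exp(−0.00493)] = 0.54 events. The chance of none is exp(−0.542) = 58%, in which case the adjusted odds ratio may not be estimable.

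**False positives.** With Fisher's exact test as a stand-in for the regression, 110 per group, 2% a year and T = 3, the rejection rate under no true difference is 47% under (a), 50% under (b) with h = 80%, and about 4% under (c) with h = 80%. With matched windows and no exclusion it is 2.6%. At T = 1 it is only 1.4% under (a), because few events occur at all.

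**The case against.** The strongest reply is that no sentence says this particular outcome is compared between groups. Its clock exists only for patients, so it may be meant as a description of the ARDS group, and a condensed article may leave event windows to a fuller document. That is possible, but it is not stated. The rule for qualitative secondary outcomes is general and makes no exception, so following it as written produces the comparison. A control window defined elsewhere would not cancel the eligibility rule, which would still deplete control events in the most recent year.

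A second reply is that control events are not all removed. Events more than 12 months old, events managed without admission (some deep venous thromboses) and events in the 90 days after inclusion can all remain. Baseline interviews and record review cover earlier health and are not limited to patients. This stands, and it is why the size depends so heavily on the undefined control window.

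A third is that the outcome is exploratory. This also stands and lowers the priority, but the label does not correct a structural bias in the estimate.

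**Conclusion.** The point holds as a bias in a secondary comparison. On a literal reading, the odds ratio is biased upward for any control window no longer than the patients'. Under a true odds ratio of 1, an assumed 2% annual rate and 50 to 80% of events admitted, it is about 1.2 to 5.0 with equal look-back and about 4 to 12 with 90 days of control observation. Only a control look-back longer than the patients' by more than h years (0.5 to 0.8 here) would reverse it, and none is described.

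A reader might go further and infer that control events are forced to zero and the odds ratio is inflated by construction. For example, 6 of 99 against 0 of 99 gives Fisher p = 0.029 and a Haldane-corrected odds ratio of 13.8, and 10 against 0 gives 23.3. The document does not support that. Control events are depleted, not eliminated, and those event counts are assumed. Even at 3% a year, 99 patients would have about 3 events in 12 months (99 × 0.0296 = 2.9), and 3 against 0 gives p = 0.25. Nor is a threefold spread in patient follow-up settled, since the document gives both 12 months and 12 to 36 months.

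This should be fixed before analysis. The DLCO comparison and its sample size are unaffected.

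**What to change.** In the Statistical analysis section, exempt this outcome from the between-group logistic regression. Report it in the ARDS group only, as incidence per 100 person-years from index discharge to the study interview, with 95% CI. State that no comparison with controls is made because control eligibility selects on these events. Reconcile the 12-month and the 12-to-36-month statements of when patients are evaluated, because they determine the person-time.

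A comparison could be kept by giving both groups one calendar window, analysing person-time and not excluding controls for events within it. That would change control eligibility and is a larger step than this outcome warrants.

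The cost is a wording change and the need for event dates, plus the loss of one exploratory between-group p-value that could not have been interpreted. No extra participants are needed.

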### Selection of centers

The participating centers will be selected after their representatives complete a questionnaire to assess feasibility. Institutions that demonstrate high potential for recruiting research participants and are in line with good clinical practice will be included, according to the following characteristics: being a reference hospital for the care of patients with COVID-19 in the metropolitan region of Porto Alegre; having an intensive care unit (10 or more beds) for the treatment of COVID-19 patients; demonstrating feasibility for the diagnosis of COVID-19 by RT-PCR or antigen testing; and accepting participation in the study by signing a cooperation agreement.

### Recruitment

The participating centers will select patients whose internal records show that they meet the inclusion criteria for participation in the study. Recruitment will be performed by face-to-face or remote interviews with the patient and/or his or her family by the research team. After they sign the informed consent form and after collection of their baseline data, the participants will be evaluated through a structured and centralized telephone interview. For ARDS/COVID-19 patients, the interview will be conducted 12 months after hospital discharge, and controls will be evaluated within 90 days after their inclusion in the study.

The participants will be included by applying the eligibility criteria, which will be recorded in the triage log. Patients who meet all the inclusion criteria and no exclusion criteria will be invited to voluntarily participate in the study by signing the informed consent form in person or electronically. The process of obtaining informed consent will be detailed in the ethics and good clinical practices section. The participant will be approached by a researcher duly trained in good clinical practice, who will maintain the anonymity and confidentiality of the data and will promote conditions of comfort for the participant.

### Data collection

At baseline, structured interviews will be applied to the study participants, and we will review their medical records to collect sociodemographic data, previous health information, and lifestyle habits before their inclusion in the study. For participants with ARDS, we will collect data on hospitalization for COVID-19, including variables related to severity (sequential organ failure assessment [SOFA], use of mechanical ventilation) and prescribed treatments (vasopressors, corticosteroids).

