### Patient selection

#### Patients with acute respiratory distress syndrome

Patients will be considered eligible if they are ≥ 18 years of age, have a positive reverse transcription polymerase chain reaction (RT-PCR) test or a positive antigen test for SARS-CoV-2 infection collected via nasopharyngeal swab during hospitalization or within 14 days beforehand, and are diagnosed with ARDS due to COVID-19 during hospitalization, and hospital discharge from the index hospitalization. The diagnosis of ARDS was defined according to the Berlin criteria:^(17)^ respiratory failure not fully explained by heart failure or fluid overload; onset within one week of the known lesion or new symptoms that worsened; bilateral opacities not fully explained by effusions, lobar collapse, lung collapse, or nodules; hypoxemia defined as the relationship between partial pressure of oxygen and fraction of inspired oxygen (PaO_2_/FiO_2_) ≤ 300mmHg, with positive end-expiratory pressure or continuous positive airway pressure ≥ 5cmH_2_O. The exclusion criteria are severe underlying disease with a life expectancy less than 3 months, unwillingness to undergo the tests to be performed, absence of a family member if the patient has communication difficulties (aphasia, cognitive impairment, nonnative speakers of Portuguese), and nonconsent to participate in the study.

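### The stated adjustment set omits smoking and height and puts no date on comorbidities, so the DLCO contrast can keep smoking confounding, and the wording allows post-ARDS diagnoses into the model

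*Protocol article*

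**What the plan says.** The Outcomes section states: "The primary outcome of the study is the pulmonary diffusing capacity for carbon monoxide (DLCO) measured after 12 months". The sample size section plans it in absolute mL/min/mmHg, and the article mentions no percent-predicted or height-standardised form.

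The Statistical analysis section states: "The primary outcome will be compared between the study groups using logistic regression adjusted for sex, age, and comorbidities". The effect measure for that model is an odds ratio. Qualitative secondary outcomes are handled the same way. Quantitative ones use "multiple linear regression adjusted for sex, age, and comorbidities" and report a difference in means. The covariate list is the same throughout and includes neither smoking nor height.

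On timing, the Data collection section dates health history and habits to the period up to inclusion: "collect sociodemographic data, previous health information, and lifestyle habits before their inclusion in the study". Cases are eligible only if they "are diagnosed with ARDS due to COVID-19 during hospitalization, and hospital discharge from the index hospitalization". The first Recruitment section adds: "Telephone contacts will be made after hospital discharge, and the eligibility criteria and the free and informed consent form will be applied". The Procedures section then says: "Teleconsultation and exams will be performed between 12 and 36 months after discharge from the index hospitalization for ARDS".

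Controls are relatives or social contacts of the cases. People with persistent COVID-19 symptoms or a non-elective admission for clinical disease in the last 12 months are excluded. No matching is described.

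**The concern.** In a non-randomised comparison, the covariate list carries most of the statistical control of confounding. Two features of this list deserve attention.

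The first is what it leaves out. Absolute DLCO varies with smoking and body size. Smoking is not a comorbidity in ordinary usage, so the existing list cannot be presumed to cover it. If smoking differs between ARDS survivors and their relatives or contacts, part of the group contrast in DLCO would reflect smoking. The same applies to the other lung and exercise outcomes.

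The second is what it might let in. Inclusion of a case comes after the ARDS episode. If comorbidities means anything diagnosed by inclusion, then kidney, heart or lung disease that began with or after that episode could enter the model as a covariate. The Discussion itself treats kidney and cardiovascular disease as possible consequences of COVID-19. Adjusting for a consequence of the exposure removes part of the effect under study.

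**Working it through.** **1. The plan's own figure.** Inputs from the sample size section: difference 2, SD 5, power 80%, significance level 5% (two-sided reproduces the figure).

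- n per group = 2 × (1.960 + 0.842)² × 5² / 2² = 98.1, rounded up to 99; total 198.
- With 10% losses: 99 / 0.9 = 110 per group.
- Power at 99 per group is 80.4% (normal approximation).

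The stated 99 and 110 reproduce. This point does not touch them.

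**2. Smoking left out.** The documents give no smoking prevalence and no effect of smoking on DLCO, so both inputs are assumptions. On a mean-difference scale, bias = prevalence gap × effect on DLCO.

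| Prevalence gap | Effect 2 | Effect 4 |
|---|---|---|
| 10 points | 0.2 | 0.4 |
| 20 points | 0.4 | 0.8 |

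Against the 2-unit target this is 10 to 40%. A wider range (gap 5 to 30 points, effect 1 to 4) gives 0.05 to 1.2, about 2 to 60%. The sign depends on which group smokes more, which the documents do not say.

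**3. Height left out.** Bias would need a height difference between groups that remains after sex and age, and nothing in the documents indicates one. The expected loss is therefore mainly precision. If the added covariates together explain 5 to 10% of the residual variance (assumption), the SD becomes 5 × √(1 − 0.05) = 4.87 or 5 × √(1 − 0.10) = 4.74. Power at 99 per group then rises from about 80% to about 82% or 84%.

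**4. Comorbidity timing.** The sections in sequence: ARDS admission, discharge, contact and consent, inclusion, with exams 12 to 36 months after discharge. The only date attached to health history is inclusion, which for cases lies after discharge. No sentence restricts comorbidities to those present before the index admission, and none says that later diagnoses will count.

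If later diagnoses did count, the part of a true difference removed would be roughly the excess frequency in cases × effect on DLCO. With an excess of 10 to 30 points and an effect of 1 to 4 (assumptions), this is 0.1 to 1.2, leaving 1.9 to 0.8 of a true 2.0.

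**5. The two together.** Assume a true total difference of −2.0. Smoking is 40% in cases and 20% in controls, with effect −2. Post-ARDS comorbidity is 35% and 10%, with effect −3. The direct part is then −2.0 + 0.25 × 3 = −1.25.

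- Crude: −2.0 − 0.20 × 2 = −2.4.
- Adjusted for smoking only: −2.0, the truth.
- Adjusted for comorbidity including later diagnoses, not smoking: −1.25 − 0.4 = −1.65.
- Adjusted for both: −1.25.

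A linear-model simulation gave the same four values. The two errors can partly offset, so the net direction cannot be read from the documents. The example also shows that adding smoking without dating comorbidities can move the estimate further from the truth.

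**The case against.** - **Scale.** The article plans an odds ratio for DLCO, so a shift in mL/min/mmHg does not measure bias in the planned primary estimate. This stands. The figures are illustrations on the scale of the sample size calculation. They apply directly only to a difference in means, which is planned for quantitative secondary outcomes. The missing covariate is a weakness under either model.
- **Timing.** A reader might infer that the plan will adjust away the sequelae it studies. The documents do not support that. Previous health information may well mean history before COVID-19, since the hospitalisation is covered in a separate sentence. Comorbidities are not defined, and their definition may stand in a full protocol or SAP that is not shown. What remains is that the one stated reference point permits the harmful reading.
- **Design.** It would be too strong to call the covariate list the only protection against bias. Drawing controls from relatives and contacts, and the exclusions applied to them, are restrictions by design. They are not matching and do not ensure balance on smoking.
- **Height.** A reader might infer that height confounds the comparison. No group difference given sex and age is shown, so the argument is about precision and standardisation.
- **Smoking data.** The article speaks of lifestyle habits without naming smoking. That it is recorded there is a reasonable reading, not a stated fact.

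**Conclusion.** The point holds as a recommended improvement to a stated model. The adjustment set is fixed as sex, age and comorbidities, in an unmatched comparison of absolute DLCO, although lifestyle data will be collected. Omitting smoking can leave confounding of unknown sign. Its illustrative size is 0.2 to 0.8 mL/min/mmHg, which rests entirely on an assumed 10 to 20 point gap and an assumed effect of 2 to 4. It would be wrong to say that confounding does remain, because the documents report no imbalance. Omitting height costs mainly precision, a few points of power at most under the assumptions above. Dating comorbidities is a cheap safeguard against a reading that the wording allows; it does not correct a demonstrated error. The sample size is unaffected.

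**What to change.** In the Statistical analysis section:

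- Add smoking status (never, former, current) to the adjustment set for DLCO and for the other lung and exercise outcomes.
- Add height, or analyse a height-standardised DLCO.
- State that the comorbidities used for adjustment are those present before the index COVID-19 admission. For controls, use a comparable reference date, such as the admission date of the linked patient. Apply the same definition to the secondary outcomes. Smoking status is best taken at the same date, since habits may change after a severe illness.

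The date and smoking changes should be made together, for the reason shown in the last step of the working.

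Cost: a wording change and a date qualifier on the comorbidity form, with medical records already being reviewed; a few degrees of freedom; and some recall effort for controls. No change in sample size is needed.
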